#### Sampling Design

A multistage cluster sampling technique is being used in this study. The first step in the sampling procedure will be to have representative data from the 6 zones (N, S, E, W, NE, and Central) of the country (Figure 1). The participating institutions from 6 zones were selected in view of location, logistics, feasibility, and the investigator profile. One urban and one rural Vidhan Sabha constituency near each institution will be selected. The choice of selection of districts and the constituencies will be given to the principal investigators at each site in order to make the study execution simpler. A rural district would mean 70% of subjects pursuing agriculture activities, while urban would mean that less than 30% have agriculture as the source of income.

After the constituencies are selected, the entire list of polling booths will be obtained from the Regional Election Commission offices. Polling booths from rural or urban constituencies will be selected to fulfill the required sample size using a random number table so that each polling booth has an equal chance to get selected. This procedure will be carried out at the coordinating center (SKIMS, Srinagar) by a third party not directly involved in the study. Next, the sites will procure the electoral roll, and voter IDs will be searched for women (aged 18-40 years) to be the potentially eligible subjects. The resulting list of women will be screened using a checklist for eligibility. If a woman is not eligible or refuses to participate in the study, the offer will go to the next woman in the list. If there is more than one eligible woman in a family, the sampling frame will also shift to the next in the voter ID list. The procedure will continue until a total of 1000 women (500 rural and 500 urban) are screened per center (Figure 2).

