**Figure 2 figure2:**
[figure not shown]
Flowchart for sampling design and workflow of the study. AE-PCOS: Androgen Excess and Polycystic Ovary Syndrome; AIIMS: All India Institute of Medical Sciences; GMC: Government Medical College; IPGMER: Institute of Post Graduate Medical Education & Research; MHRT: Maternal Health & Research Trust; NEIGRIHMS: North Eastern Indira Gandhi Regional Institute of Health and Medical Sciences; NIH: National Institutes of Health; NIRRH: National Institute for Research in Reproductive Health; OMC: Osmania Medical College; PCOS: polycystic ovary syndrome; PGIMER: Postgraduate Institute of Medical Education and Research; SKIMS: Sher-i-Kashmir Institute of Medical Sciences.

#### Estimation of Sample Size for Substudy 1

Sample size was calculated, primarily to estimate the prevalence of PCOS in the country. Previously reported prevalence rates of PCOS have varied from 3.7% to 22.3% [32,33]. For the purpose of calculation of sample size, we presume the prevalence of PCOS in India to be 10%. With an assumed prevalence of 10% and an absolute error margin of 1% in a 95% 2-sided confidence interval and making allowance for about 20% refusals or nonresponse, we need to target a total of 4500 women. Further, being a cluster design and taking a design effect of 2, a total of 9000 women aged 18-40 years will be studied from 10 centers (ie, 1000 per center, except for the 2 centers in Hyderabad, which have been designated with 500 each), half from a rural community and half from an urban community at each center.

Based on a pilot study previously conducted by the chief coordinator using a similar questionnaire [34], 30% (2700/9000) of the women are expected to screen positive (likely to have PCOS) on the screening questionnaire and therefore are required to be investigated in detail. Additionally, of the 70% (6300/9000) of women expected to screen negative on the screening questionnaire, 20% (1260/6300) will require examination and investigation in detail. This will make the sample size of women requiring detailed evaluation and blood testing a total of 3960 (N=2700+1260). Keeping in view the number of centers (N=10), each participant center will screen approximately 1000 women, and a total of 440 women who will be invited for detailed examinations: 20% (140/700) of screen-negative women and all 30% (300/1000) who screen positive (Figure 2).

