#### Field Activities

Field activities will be conducted for the purposes of screening. It will include rapport building among locals and the selection of the study subjects (1 woman per household). It will be the duty of the research staff to approach the selected individuals and to make them understand their role in the study. Consenting individuals will be screened for PCOS phenotype using the predesigned structured questionnaire. The screening questionnaire will be used to obtain information on personal identification details, demographics, socioeconomic status, menstrual history and clinical information, history of any systemic disease, and QOL. The women who have hyperandrogenism or oligomenorrhea with or without obesity and acanthosis nigricans (IR) will be taken as probable cases of PCOS. Screen-positive and selected screen-negative (regular menstrual cycles, no features of hyperandrogenism or insulin resistance) individuals will be informed to visit the hospital for further investigations.

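### One woman is taken per household while working down the voter list, with no random choice within the household, so selection chances for the prevalence estimate are unequal and appear to depend on list position

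*Protocol article*

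**What the plan says.** Under Sampling Design, polling booths are drawn with a random number table so that booths have equal chances. Within a chosen booth, women aged 18-40 are found on the electoral roll and checked for eligibility. If a woman is ineligible or refuses, the offer passes to the next name. For families the rule is: "If there is more than one eligible woman in a family, the sampling frame will also shift to the next" name on the roll. This continues until each center has its rural and urban quota.

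Field Activities repeats the cap, describing "selection of the study subjects (1 woman per household" as part of the field work. Neither section says which woman in a family is kept, or that she is drawn at random.

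The target is set under Estimation of Sample Size for Substudy 1: "we presume the prevalence of PCOS in India to be 10" percent, with "an absolute error margin of 1% in a 95% 2-sided confidence interval".

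Statistical Analysis lists general summaries and tests. It gives no estimator for prevalence, weighted or unweighted.

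**The concern.** National prevalence is the first primary objective, and the article promises representative data. Random selection is used for the booths but is not described at the last stage, where individual women are chosen. With one woman per home, a woman living with other eligible women has a smaller chance of entering the sample than a woman living with none. If names are taken in list order, the chance also depends on where she stands on the roll.

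Neither feature matters if prevalence is the same across household types and list positions. If it is not, the estimate is shifted, and enrolling more women does not reduce the shift. The design effect of 2 allows for extra variance from clustering. It makes no allowance for bias.

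The choice is made in the field. An analysis plan can weight for household size if the count was recorded, but it cannot make a list-order choice random afterwards.

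**Working it through.** **1. The plan's own figure.** The inputs are in Estimation of Sample Size for Substudy 1: prevalence p = 0.10, margin d = 0.01, 95% two-sided confidence, "making allowance for about 20% refusals or nonresponse", design effect 2. The formula is n = z²p(1−p)/d².

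- With z rounded to 2: 4 × 0.10 × 0.90 / 0.0001 = 3600; 3600/0.8 = 4500; × 2 = 9000. This matches "we need to target a total of 4500 women" and "taking a design effect of 2, a total of 9000 women aged 18-40 years will be studied from 10 centers".
- With z = 1.96: 3457.3; /0.8 gives 4322; × 2 = 8644, about 4% lower.

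The stated size is reproduced and does not depend on the household rule. The 1-point margin is the yardstick below.

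**2. Selection chance.** If a home has k eligible women and one is taken, their average chance is 1/k of that of a woman who is the only one in her home.

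**3. Share in the sample.** The documents give no household composition, so this is an assumption: a share s of eligible women live in two-woman homes. In an unweighted sample their share is s′ = (s/2)/(s/2 + 1 − s).

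**4. Bias in prevalence.** Bias = (s′ − s) × gap, where gap is the prevalence in two-woman homes minus that in one-woman homes (assumed 3 to 5 points).

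| s | s′ | Bias, gap 3 | Bias, gap 5 |
|---|---|---|---|
| 0.30 | 0.176 | −0.37 | −0.62 |
| 0.40 | 0.250 | −0.45 | −0.75 |
| 0.50 | 0.333 | −0.50 | −0.83 |

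Example: s = 0.40 with 13% and 8% prevalence. The true value is 0.4 × 13 + 0.6 × 8 = 10.0%. The sample value is 0.25 × 13 + 0.75 × 8 = 9.25%.

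**5. How far this depends on the assumed gap.** The example is a prevalence ratio of 13/8, about 1.6. At a true prevalence of 10% and a ratio of 1.2, prevalence in one-woman homes is 10/(1 + 0.2s). The gap is then 1.8 to 1.9 points and the bias −0.23 to −0.30. With no gap it is zero. With gaps of −3 to −5 it is +0.37 to +0.83.

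A wider grid takes a share h of 10-50% of households with k = 2 or 3 eligible women. Such women are kh/(1 − h + kh) of the population but h of the sample, so they appear at 0.40-0.75 of their true share.

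| Prevalence ratio, multi-woman to other homes | Bias (points) |
|---|---|
| 0.8 | +0.2 to +0.6 |
| 1.0 | 0 |
| 1.2 | −0.2 to −0.5 |
| 1.5 | −0.4 to −1.0 |
| 2.0 | −0.7 to −1.7 |

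**6. List order by itself.** Assume each two-woman home has one younger woman (12%) and one older (8%), and one-woman homes average 10%. If the older is always taken, the estimate is (1 − h) × 10 + h × 8 = 10 − 2h. That is −0.4 points at h = 0.2 and −0.8 at h = 0.4. If the younger is always taken, the signs reverse. With a random choice the bias from order is zero.

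**7. Price of weighting.** With weights 1 and 2, the Kish factor is (1 + 3h)/(1 + h)², where h equals s′. For s′ = 0.176, 0.250 and 0.333 it is 1.10, 1.12 and 1.13 (rounded). A 1-point half-width becomes about 1.05-1.06 points. Over the wider grid the factor is about 1.07-1.33.

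**The case against.** Taking one woman per household is a legitimate way to limit clustering, and the cap itself is not at fault. The article is also a condensed account, and four stronger readings of it do not hold.

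- **That the estimate will be unweighted.** The article is silent. Survey weights are commonly left to the full protocol or analysis plan, which are not shown, so their absence here is no fault.
- **That younger women are lost and prevalence comes out too low.** Nothing describes who lives in multi-woman homes or how names are ordered within a household. Step 6 shows that the sign turns on who is listed first.
- **That later-listed women have no chance at all.** When an earlier-listed woman is ineligible or refuses, the offer moves on, so a later one can be reached.
- **That risk-factor associations are biased.** Unequal selection by household type or age does not by itself distort an association. That would need selection related to both exposure and outcome, or effect modification.

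It is also fair to say that list position is an inference. The wording could be read as passing over the whole family, which would exclude multi-woman homes altogether. And the 30-50% and 3-5 point figures are assumptions chosen in one direction.

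What stands against all this is the stated selection rule: one woman per home, moving down a list, with no random draw described. That is a field procedure, and an analysis plan cannot undo it.

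**Conclusion.** The point holds as a fault in the selection rule for the primary prevalence estimate. Women in homes with several eligible women have a lower chance of selection, which on the natural reading depends on list position. If prevalence varies with either, the estimate is biased.

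Direction and size cannot be determined from the documents. The 0.4-0.8 point figure is material against a 1-point margin, but it rests wholly on the assumed household shares and prevalence gap. In the wider grid the shift is at most about 0.6 points for prevalence ratios of 0.8-1.2, and it reaches 1 point only at ratios of about 1.5 to 2. Weighting by household count would remove the household-size part of any bias, but not the part due to list order.

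**What to change.** **Remaining recruitment.** State in Sampling Design which woman is taken. Group the roll's women aged 18-40 by household, apply the eligibility checklist, and choose one eligible woman at random. Record the number of eligible women as confirmed by the checklist, because the roll shows only potential eligibility (pregnancy, lactation, drug use and residence are not on it). Weight the prevalence estimate by that count, capped if needed.

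**Women already enrolled.** The Results section says that recruitment began in 2018 and was expected to end in October 2021, so many may already be in. Attach the number of women aged 18-40 in each household from the roll as an approximation. Report a weighted estimate, standardized to the roll's age distribution, as a sensitivity analysis. State that this does not fully remove the effect of list-order selection.

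**Cost.** The change needs a revised field instruction, one recorded variable, and eligibility checks on more than one woman in some homes. The retrospective part uses rolls that the sites already procure. The loss of precision is small: a variance factor of about 1.10-1.13 under the two-woman-home assumptions, and up to about 1.33 in the wider grid.

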**Figure 2 figure2:**
[figure not shown]
Flowchart for sampling design and workflow of the study. AE-PCOS: Androgen Excess and Polycystic Ovary Syndrome; AIIMS: All India Institute of Medical Sciences; GMC: Government Medical College; IPGMER: Institute of Post Graduate Medical Education & Research; MHRT: Maternal Health & Research Trust; NEIGRIHMS: North Eastern Indira Gandhi Regional Institute of Health and Medical Sciences; NIH: National Institutes of Health; NIRRH: National Institute for Research in Reproductive Health; OMC: Osmania Medical College; PCOS: polycystic ovary syndrome; PGIMER: Postgraduate Institute of Medical Education and Research; SKIMS: Sher-i-Kashmir Institute of Medical Sciences.

#### Estimation of Sample Size for Substudy 1

Sample size was calculated, primarily to estimate the prevalence of PCOS in the country. Previously reported prevalence rates of PCOS have varied from 3.7% to 22.3% [32,33]. For the purpose of calculation of sample size, we presume the prevalence of PCOS in India to be 10%. With an assumed prevalence of 10% and an absolute error margin of 1% in a 95% 2-sided confidence interval and making allowance for about 20% refusals or nonresponse, we need to target a total of 4500 women. Further, being a cluster design and taking a design effect of 2, a total of 9000 women aged 18-40 years will be studied from 10 centers (ie, 1000 per center, except for the 2 centers in Hyderabad, which have been designated with 500 each), half from a rural community and half from an urban community at each center.

Based on a pilot study previously conducted by the chief coordinator using a similar questionnaire [34], 30% (2700/9000) of the women are expected to screen positive (likely to have PCOS) on the screening questionnaire and therefore are required to be investigated in detail. Additionally, of the 70% (6300/9000) of women expected to screen negative on the screening questionnaire, 20% (1260/6300) will require examination and investigation in detail. This will make the sample size of women requiring detailed evaluation and blood testing a total of 3960 (N=2700+1260). Keeping in view the number of centers (N=10), each participant center will screen approximately 1000 women, and a total of 440 women who will be invited for detailed examinations: 20% (140/700) of screen-negative women and all 30% (300/1000) who screen positive (Figure 2).

### Evaluation Methods

Both the subgroups of women coming from the community pool and institutional pool will be evaluated as per the defined protocol for clinical, biochemical, and hormonal assessment during the second to the seventh day of the cycle. In the institutional pool, women attending endocrinology, gynecology, dermatology, or other related clinics for symptoms and signs of PCOS will be asked to report to the research staff or PCOS station for detailed evaluation as per the common protocol. Support will be obtained from the public health system for enrolling women from the community and conducting further examinations, investigations, and follow-up at their facilities in urban and rural areas. All those women who are drug-naïve will undergo clinical assessment (anthropometry, hirsutism scoring, acne, oligomenorrhea, androgenic alopecia, primary infertility), biochemical evaluation (liver function test, kidney function test, lipids, oral glucose tolerance test [OGTT]), high-sensitivity C-reactive protein (hsCRP) and cytokine tests (selected cases), 25-hydroxyvitamin D [25OHD] testing (selected cases), and hormonal estimations (thyroxine [T_4_], thyrotropin, luteinizing hormone [LH], follicle-stimulating hormone [FSH], prolactin [PRL], cortisol, anti-Müllerian hormone [AMH], dehydroepiandrosterone sulfate [DHEAS], 17-hydroxyprogesterone [17OHP], sex hormone–binding globulin [SHBG], serum total testosterone and insulin at 0, 30, and 120 minutes, estradiol [E2], progesterone [P4], procollagen type I N-terminal propeptide, CrossLaps, anti–thyroid peroxidase, ferritin, B_12_, pro–brain natriuretic peptide, and C-peptide levels). The blood samples will be transported in a cold chain to one center (SKIMS, Srinagar) for lab analysis using electrochemiluminescence immunoassay (ECLIA; Roche Diagnostics USA). Analytes such as SHBG and serum total testosterone levels will be transported to one center (SKIMS, Srinagar) for purposes of uniformity and will be analyzed in one go. In a subset of cases (n=100), total testosterone and SHBG will be assayed by ECLIA and liquid chromatography–tandem mass spectrometry in the Department of Endocrinology, AIIMS, New Delhi.

The 1990 National Institutes of Health (NIH) consensus conference criteria will be taken as the qualifying criteria. This necessitates the presence of the following 2 criteria: (1) oligoovulation or anovulation (intermenstrual interval ≥35 days, presence of ≤8 cycles per year, or both) and (2) clinical signs, biochemical evidence, or both of hyperandrogenism after ruling out disorders with similar clinical presentation such as hyperprolactinemia, Cushing syndrome, congenital adrenal hyperplasia, and androgen-secreting tumors with specific laboratory analysis (cortisol, 17OHP, and DHEAS). To compare, the 2003 Rotterdam criteria and the 2009 Androgen Excess and PCOS (AE-PCOS) Society criteria will also be employed. Therefore, US examination to satisfy the diagnosis of PCOS by these criteria will be done. A common standard operating procedure for abdominal examination (liver, pancreas, ovary, and uterus) will be adhered to with a built-in system to minimize interobserver and equipment variations. The 2003 Rotterdam criteria necessitate the presence of 2 of the following 3 criteria: (1) oligoovulation, anovulation, or both; (2) clinical signs, biochemical evidence, or both of hyperandrogenism; and (3) polycystic ovary in US. The 2009 AE-PCOS Society criteria necessitate the presence of the following criteria: (1) oligoovulation and/or anovulation (intermenstrual interval ≥35 days, presence of ≤8 cycles per year, or both) and/or polycystic ovary in US and (2) clinical signs, biochemical evidence, or both of hyperandrogenism. To exclude etiologies that could mimic PCOS like Cushing syndrome, late-onset adrenal hyperplasia, or androgen-producing neoplasm, we will exclude thyroid disorders, renal hyperplasia, hyperprolactinemia, and late-onset congenital adrenal hyperplasia by medical history and hormone tests. This will further serve to unravel various comorbidities such as AGT, metabolic syndrome, IR, cardiovascular risk, psychiatric morbidities, and impairment of QOL (Figure 3). Besides, these women will be evaluated for risk factors such as birth weight, parental history of gestational diabetes or PCOS, risk of low birth weight, precocious pubarche, prepubertal obesity, antiepileptic drug intake, familial association with lifestyle diseases, etc. Abdominal MRI for comparing ovarian morphology will also be done at a selected center (SKIMS, Srinagar) using the predesigned uniform protocol.

**Figure 3 figure3:**
[figure not shown]
Study design and workflow chart of substudy 2. OGTT: oral glucose tolerance test; SGOT: serum glutamic oxaloacetic transaminase; SGPT: serum glutamic pyruvic transaminase; QOL: quality of life; USG: ultrasonography; WHO: World Health Organization.

### Study Tool: The Questionnaire

In this study, structured questionnaires will be used for capturing information. The eligibility and screening questionnaires comprise 7 and 43 questions (part 1), respectively. The screening questionnaire comprises three sections: (1) personal details, (2) menstrual history and clinical information, and (3) history of any systemic diseases. Part 1 of the questionnaires will be filled at the field site to check eligibility and identify probable PCOS on the basis of positive responses to questions. The subjects who test positive on the questionnaire (ie, probable PCOS) and 20% of those who test negative (healthy women) will be invited to the respective institutes for detailed clinical assessment. The questionnaire stands pilot-tested and modified after several rounds of investigator meetings.

### Clinical Assessment

#### History

The subjects will be invited to nearby institutes for detailed clinical, biochemical, hormonal, and sonography assessments. These women will be assessed for clinical detail about menstruation (regularity, duration, flow, amenorrhea), weight gain, unwanted male pattern hair growth, hair fall, infertility, etc. The details about any illness will be recorded. Psychiatric morbidity will be assessed using the *Diagnostic and Statistical Manual of Mental Disorders* (Fourth Edition) criteria with the Mini-International Neuropsychiatric Interview, version 4.0. The details of family pedigree will also be recorded in the predesigned questionnaire.

#### Examination

Anthropometric assessment including measurement of height, weight, waist circumference, skinfold thickness on dorsum of hand and triceps, and blood pressure and detailed systemic examination will be undertaken. Height and weight will be measured with subjects in light clothes and without shoes, using standard apparatus. Weight will be measured to the nearest 0.1 kg on a calibrated digital scale. Height will be measured by stadiometer by standard methodology to the nearest 0.1 cm. Waist and hip circumference will be measured to the nearest 0.5 cm with a measuring tape. The waist circumference will be defined as the point midway between the iliac crest and the costal margins (lower ribs), while hip circumference will be defined as the widest circumference over the buttocks and below the iliac crest [35]. Body mass index (BMI) will be derived as weight in kg divided by the square of height in meters. Overweight will be defined using the Asian BMI range of 23.0-24.9 kg/m^2^, while obesity will be defined as having a BMI equal to or greater than 25 kg/m^2^ [36]. Quantitation of hirsutism by a single observer by counting 9 specific body areas for the Ferriman-Gallwey score and assessments of acne vulgaris, androgenic alopecia, and acanthosis nigricans will be performed in all subjects [37].

